## Economic evaluation

Data on health economics will be analysed by the team at Bangor University led by [name] [name]. From an NHS perspective, we will undertake a cost-consequences analysis presenting the outcomes and cost in disaggregated form. We will collect outcome data (e.g. scores of quality corneal images and length of acquisition time of the new OCT device and the existing OCT device) for the 3 groups of participants at baseline, month 3 and month 6. Liaising with The LUHFT staff, we will calculate the cost of performing eye test per visit per participant using our LiveOCT device and the existing OCT device (if necessary) respectively. Lessons learnt from this observational study will provide guidance to inform further research including a plan for an economic evaluation alongside a future randomised controlled trial.

**Micro-costing analysis**

We will undertake a micro-costing of the introduction of the LiveOCT device into clinic based on our previous use of micro-costing. We will explore what there is to be learnt from recent developments in micro-costing in health economics and in time-driven activity-based costing as part of the value-based health care movement.

In order to undertake our cost-consequence analysis we will collect data at baseline, 3 and 6 months. See table 2.

**Table 2:** Draft plan for preliminary health economics data collection

| **No.** | **Data** | **Details** |
| --- | --- | --- |
| **Intervention delivery data** | | |
| 1. | Staff | Type of staff (i.e. type of healthcare professional), number & grade of staff who prepare, conduct the imaging, analyse scan, provide feedback to patients regarding scan and present in the imaging room for each patient’s OCT imaging appointment for both standard and new OCT imaging at each study time-point. |
| 2. | Duration of time taken for… | Preparatory, administration, conducting the imaging, analysis of the scan and feeding back to patients regarding scan for each patient’s OCT imaging appointment for both standard and LiveOCT imaging at each study time-point. |
| 3. | Disposable items | What are the disposable items and total quantity of each item for both standard and new OCT imaging? |
| 4. | Overheads | What are the relevant overheads to be charged for the department/hospital for both standard and new OCT imaging? |
| **Outcome measures -** | | |
| 5. | Primary - Quality corneal images score | What is the score of quality corneal images for each patient’s corneal image produced by standard OCT device and LiveOCT device at each study time-point? |
| 6. | Secondary – Patient’s experience, staff experience | We are aware that the main clinical study is collecting data on these. |

We will undertake deterministic sensitivity analysis to explore implications of for example various costs of the LiveOCT device and any time and motion implications of any additional time in clinic taken relating to the introduction of the LiveOCT device.

1. Data management

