### Secondary objectives

- To evaluate repeatability, sensitivity and specificity of the LiveOCT device.
- To evaluate costs and consequences- from an NHS perspective we will explore the costs and consequences of the LiveOCT device as compared to usual care.
- To study patient experience on LiveOCT device.

1. Study design

This study will follow a prospective observational study design. The single study site is St. Paul’s Eye Unit, The Liverpool University Hospitals NHS Foundation Trust (LUHFT).

Following recruitment, eligibility assessments and consent, participants will undergo a baseline assessment. Follow up assessments will take place after 3 and 6 months.

During each visit, the participant will undergo standard eye examinations (visual acuity and slit-lamp bio microscopy), and non-invasive tests including endothelial cell counting (ECD), tomography, and OCT imaging by standard OCT devices (TOMEY CASIA SS-1000 and Heidelberg Spectralis) and our new LiveOCT device variants (D1 and D2). Two qualified individuals, both operating one of two LiveOCT devices equipped with the study software, will perform the study device measurements. Each patient will be measured three times with each device at both the baseline and at follow-up visits (after 3 and 6 months). See figure 1 for the study design showing the study design/ patient pathway.

We expect the duration of D1 and D2 assessments (capturing 3 images on each device per visit) to take 15 minutes for each device, so 30 mins in total will be dedicated to our novel OCT devices each visit. The order of the OCT devices will be randomised using a random permutation approach to avoid bias through patient or investigator fatigue but the all measurements on each device will take place at the same time as to avoid delays caused by positioning the patient.

   
[figure not shown]

Figure 1. Schematic of the Study design/ patient pathway

1. Study setting

The Study will run in a single site at the Clinical Eye Research Centre (CERC) in St. Paul’s Eye Unit within The Liverpool University Hospitals NHS Foundation Trust (LUHFT).

1. Study participants

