## Baseline and subsequent assessments

For each participant, there will be 3 visits: baseline, month 3 and month 6. During each visit, the participant will undergo standard eye examinations (visual acuity and slit-lamp bio microscopy), and non-invasive tests including endothelial cell counting (ECD), tomography, and OCT imaging by standard OCT devices (TOMEY CASIA SS-1000 and Heidelberg Spectralis) and our new LiveOCT device variants. Two qualified individuals, both operating one of two LiveOCT devices equipped with the study software, will perform the study device measurements. Each patient will be measured three times with each device at both the baseline and at follow-up visits. A questionnaire will be completed on their experience and view of the device at the end of each visit.

The following procedures will be carried out on each patient at baseline, month 3 and month 6, as shown in Table 1:

1. Eye examinations (visual acuity and slit-lamp bio microscopy)
2. Endothelial cell counting (ECD) with confocal microscopy
3. Tomography with Pentacam camera
4. OCT imaging with devices currently in clinic (The TOMEY Casia and Heidelberg Spectralis)
5. Imaging by our new LiveOCT device – variant 1 (D1) and 2 (D2)
6. Patient experience questionnaire

The order of the OCT devices will be randomised using a random permutation approach to avoid bias through patient or investigator fatigue but the all measurements on each device will take place at the same time as to avoid delays caused by positioning the patient.

All the procedures except for imaging with our new LiveOCT device are part of standard care. For patients with keratoconus, all the three visits are standard patient care pathway. For patients with FECD, month 3 visit is an additional visit to the standard care. For healthy volunteers, all the 3 visits will be research activities.

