## Secondary outcomes

**Repeatability/reproducibility:** Outcome metrics will be the repeatability and reproducibility of measurements (identification and thickness) of structural parameters of the cornea, corneal surface contour and refractive power.

**Sensitivity and specificity:** We will use published grading systems specific to the two main conditions of FECD and keratoconus. For keratoconus, the sensitivity of the LiveOCT will be assessed by its ability to detect the same diagnostic parameters of non-uniform and focal corneal thinning and irregular and non-asymmetric anterior and posterior corneal profiles currently measured using the Pentacam. For FECD, the sensitivity of the LiveOCT will be assessed by its ability to measure increases in corneal thickness and areas of corneal swelling, and excrescences (guttata) and thickening of Descemet's membrane in patients who have guttata evident with slit lamp bio microscopy and increased corneal thickness measured with the Pentacam. Specificity will be defined as the percentage in which the described diagnostic changes in the cornea for keratoconus and FECD are not apparent with the LiveOCT device.

**Patient experience:** Study participants will be asked to fill in a simple set of questions concerning their experience with the LiveOCT devices. The patients will be asked to fill out paper copies of the questionnaire after the end of each study appointment, but the study nurse will be available to help if required.

If the participant indicates that they are feeling particularly anxious or depressed on the questionnaire, a member of their care team will pass this information onto their GP.

**Cost Effectiveness:** See 13.3 - economic evaluation

1. Definition of end of study

The study will be completed and terminated on 31st October 2022, which is defined to be the date when analysis of the data collected during the trial is being completed.

Suspension or early termination of the study when there are serious concerns about subjects’ safety and inadequate performance, that cannot be mitigated by modifications of the study protocol based upon the review of the safety data.

1. Discontinuation/ withdrawal of participants from study treatment

If a decision is made by the participant and or/clinician not to continue with the study, the participant will be removed from it and the event recorded. Data will still be collected unless the participant explicitly withdraws consent for it.

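### Table 2 relies on the main study for patient and staff experience, but the protocol describes patient experience for LiveOCT only and no source for staff experience

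*Protocol*

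**What the plan says.** Under Secondary objectives, the economic aim is comparative, although worded as exploration: "from an NHS perspective we will explore the costs and consequences of the LiveOCT device as compared to usual care". A separate bullet sets the patient-experience aim with no comparator: "To study patient experience on LiveOCT device".

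In the Micro-costing analysis section, Table 2 lists the data for the cost-consequences analysis. Row 6 reads "Secondary – Patient’s experience, staff experience" and gives as its only detail "We are aware that the main clinical study is collecting data on these".

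The main study describes one instrument. Baseline and subsequent assessments says "A questionnaire will be completed on their experience and view of the device at the end of each visit". Secondary outcomes says "Study participants will be asked to fill in a simple set of questions concerning their experience with the LiveOCT devices". The next paragraph there shows that the form may also reveal mood, since it provides for action "If the participant indicates that they are feeling particularly anxious or depressed on the questionnaire".

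**The concern.** The economic plan assigns the collection of two consequences to the main study, and the main study as described does not fully provide them. Health economics data are analysed by a team at another university, which depends on what the clinical site collects.

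If patients are asked only about LiveOCT, a favourable score cannot be read as better or worse than their experience of standard OCT. If nobody asks staff, that row of the results table stays empty. The gap is one of data collection. An analysis plan can decide how to summarise answers, but it cannot supply answers to questions that were not put. The protocol also intends this study to guide an economic evaluation alongside a later randomised trial, so a missing comparator would carry forward.

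**Working it through.** The protocol states no figure on this point, so the check is to ask, for each planned consequence or cost item, whether data are described for LiveOCT and for standard OCT.

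| Item | Where described | LiveOCT | Standard OCT |
| --- | --- | --- | --- |
| Staff type, number and grade | Table 2, row 1 | yes | yes |
| Time taken | Table 2, row 2 | yes | yes |
| Disposables | Table 2, row 3 | yes | yes |
| Overheads | Table 2, row 4 | yes | yes |
| Image quality score | Table 2, row 5; Economic evaluation | yes | yes |
| Acquisition time | Economic evaluation | yes | yes |
| Patient experience | Table 2, row 6; Secondary objectives; Baseline and subsequent assessments; Secondary outcomes | yes | none described |
| Staff experience | Table 2, row 6 only | none described | none described |

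**Patient experience.** The objective, the procedure and the outcome definition all refer to LiveOCT or to the device in the singular. None describes a question about the Casia or the Spectralis. The mood response is given on a form completed once, after the whole appointment, so it cannot be attributed to one imaging method.

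**Staff experience.** The term does not appear in the objectives, the visit procedures, Table 1, the outcomes or the list of CRF topics. The CRF is defined per research subject, so its silence alone would prove little. The silence of every other section is what leaves row 6 without a source. Rows 1 and 2 do record staff, but as resource use.

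**Volume.** Planned participants are 40 + 30 + 20 = 90, with 3 visits each and one form per visit: 90 x 3 = 270 forms at most, before dropout. These are up to three repeated ratings from each of 90 people, not 270 independent observations. The product shows how many forms could carry a matched item. It does not measure bias or lost precision.

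**Whether a comparison is feasible.** Each participant has both standard OCT devices and both LiveOCT variants at every visit, with the order of OCT devices randomised. Within-person ratings could therefore be obtained without any extra procedure.

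**The case against.** The strongest reply is that patient experience contradicts nothing. It has its own objective, which names LiveOCT and no comparator, and the questionnaire matches it. The usual-care wording belongs to a different bullet and promises only exploration. The analysis is to be presented in disaggregated form, so a consequence may properly be reported for LiveOCT alone, and Table 2 is labelled a draft, preliminary plan. All of this stands, and it keeps the point minor. It does not give row 6 a comparator, and the protocol does not say that the row will be one-sided.

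The questionnaire is not among the documents either. A one-line summary need not list every item, and the mood response shows that this one does not. The protocol also refers to a data management plan that is not shown. A reader might infer that the form certainly holds no standard-OCT item and that no staff-experience record will exist. The documents do not support that certainty. They support only that none is described.

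Three other strong readings should be resisted:

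- **No staff data at all.** A reader might conclude this, but Table 2 collects staff type, number, grade and time for both methods.
- **The cost-consequences analysis fails.** Costs, time and image quality still have both sides.
- **A single end-of-visit form cannot separate LiveOCT from the day's other tests.** Items worded about LiveOCT would largely do so. That argument applies only to general items such as mood.

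**Conclusion.** The point holds in a limited form and is minor. Row 6 relies on the main study for two consequences. For one of them, patient experience, the main study as described provides LiveOCT data only, so it can be described but not compared with standard OCT. For the other, staff experience, no source is stated for either method. The primary outcomes and the remaining economic items are unaffected.

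This rests on two assumptions: that the protocol's description of the questionnaire is a fair account of its content, and that no staff instrument is set out in a document not shown. If either is wrong, the remedy for that part reduces to a sentence saying where the data are collected.

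**What to change.** **Patient experience.** In Baseline and subsequent assessments and in Secondary outcomes, add to the existing questionnaire the same device-specific items for the Casia and the Spectralis as are asked for LiveOCT. Keep the two standard devices separate, because there is no single standard OCT. Summarise within-participant differences and allow for repeated visits. The cost is an amended form and a minute or two more per participant per visit. If this is not wanted, state in the Economic evaluation section and in Table 2 that patient experience is descriptive for LiveOCT only, which costs one sentence.

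**Staff experience.** Either delete it from Table 2, row 6, or collect a short descriptive rating from whoever operates each device and say where it is recorded. Do not present that rating as a comparison between devices. The two named operators are described only as running LiveOCT, and the Statistical analysis plan section itself notes that operator is confounded with device.

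Either change to the forms has to be made before data collection to be of full use.

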## Data collection tools and source document identification

All activities will be in line with local practices, ICH GCP, the Caldicott Guardian and the Data Protection Act 2018, UK’s implementation of the General Data Protection Regulation (GDPR).

All research subjects will be pseudo-anonymised by assigning a unique study ID to index all the data. Data that are collected for each research subject constitute correspondingly his/her CRF (Case Reports Form), which will cover the following areas/topics:

• Inclusion criteria and consent

• Demographics

• Medical history

• Medication

• Surveys and questionnaires

• Adverse events

• Binary files (images)

At the end of each appointment the study nurse will check the CRFs for completeness before the participant leaves so that tests can be completed if required. If an omission is noticed after the participant has left they will be asked to return if reasonably possible within a week of the initial appointment. Any major corrections or major missing data such as age, gender, type of disease, images not taken, incorrect recording of visual acuity will be noted and corrected by the research nurse.

Only NHS research staff working on this project will have access to the patient identifiable data. No patient identifiable data will be transferred out of the Trust. Only pseudonymised data will be transferred out of the Trust (transferred using encrypted portable hard drive to the University research team for analysis).

For the new LiveOCT device, data will be collected by the device software on its PCs device. The encrypted data will be synchronised between LiveOCT devices and an encrypted external hard drive and backed up using a dedicated external hard drive every evening. The external hard drives will be kept in a secure location. The PCs will also have a windows user account access control. For all stored data, raw image data will not be encrypted but not stored in a manner identifiable to a patient. Encrypted note files will be created for each “visit” but not stored in a manner identifiable to a patient. An encrypted database will link image data and encrypted notes to patients, and store patient identifiable details (only names for validating patient ID in use). Each participant will be assigned an anonymous study number. Project software will be required to read encrypted database data and files and software access will be controlled by valid username and password access. User names will only be issued to authorised project members and staff employed on the clinical study. Software can produce unencrypted pdf reports of individual patients for clinical purposes if needed. For study purposes, export of data for analysis has patient identifiable data (excluding study ID) and notes removed. The spreadsheets containing the data will be locked every 3 months. All exported data will further be secured on encrypted drives only.

For further information please see our comprehensive data management plan and other associated documents (referred to in our data management plan).

## Access to data

Identifiable information will only be accessed by the authorised research team at the NHS research site. Any participant information (e.g. images and questionnaires) will be pseudo-anonymised within the LUHFT before being transferred to the universities for analysis, and stored securely at the university’s secured network drive. Pseudo anonymised data related to health economics analysis will be shared with [name] [name] at Bangor University.

## Archiving

Data collected, required software to read and associated analyses will be deposited in a data archive at the end of the project and stored for 15 years.

Frequent backups are performed using the best enterprise backup solutions at LUHFT as well as UoL, and are physically stored in a fire-proof safe. The backup strategy will be implemented to support hourly, daily, monthly and yearly retention.

1. Monitoring

Study monitoring will be carried out to ensure that the rights and well-being of the participants are protected during the study. A risk assessment will be performed prior to initiation. This will be completed in partnership with representatives of the study sponsor, the Chief Investigator, the Clinical Lead and the Study Manager.

The study will be managed by an Executive group, which will meet face-to-face 3 to 4 times per year and by teleconference approximately fortnightly. The Executive group for the study will be chaired by the Chief Investigator and will consist of the applicants and the trial manager.

The study will be overseen by a study steering committee that will be convened before the start of recruitment.

Membership of the study steering committee will include:

- Independent chair ( [name], Consultant Ophthalmologist at The Royal Liverpool University Hospital)
- Independent Patient representative ([name], ED Society)
- Independent Clinical Representative ([name], Consultant Ophthalmologist at The Royal Liverpool University Hospital)Study representative ([name], Chief Investigator) – non independent member

The steering committee will check that we are adhering to protocols and recording data and adverse events appropriately and accurately at month 3 and month 6 of the study.

1. Ethical and regulatory considerations

## Approvals

## All approvals (NRES, MHRA Notice of No Objection and HRA) will be in place before we commence recruitment. Adverse event and safety reporting

*The research team do not expect there will be any AE or SAE, however, in the event they do occur, the procedures below will be followed.*

Definitions from the ‘Guidelines on Medical Devices’ from the European Commission (‘Clinical investigations: serious adverse event reporting under directives 90/385/EEC and 93/42/EEC’) and the examples that would apply to the LiveOCT study are presented in the table below

| **Term** | **Definition** | **Example(s) applying to LiveOCT.** |
| --- | --- | --- |
| Adverse Event (AE) | Any untoward medical occurrence, unintended disease or injury or any untoward clinical signs (including an abnormal laboratory finding) in subjects, users or other persons whether or not related to the investigational medical device.  NOTE 1: This definition includes events related to the investigational device or the comparator.  NOTE 2: This definition includes events related to the procedures involved.  NOTE 3: For users or other persons, this definition is restricted to events related to investigational medical devices. | Irritation of forehead chin/ hands in contact with device.  Irritation of eye from Laser  Trapping of fingers in device |
| Serious Adverse Event (SAE) | Adverse event that:  a) led to a death, injury or permanent impairment to a body structure or a body function.  b) led to a serious deterioration in health of the subject, that either resulted in:  - a life-threatening illness or injury, or  - a permanent impairment of a body structure or a body function, or  - in-patient hospitalization or prolongation of existing hospitalization, or  - in medical or surgical intervention to prevent life threatening illness  c) led to foetal distress, foetal death or a congenital abnormality or birth defect.  NOTE 1: Planned hospitalization for pre-existing condition, or a procedure required by the Clinical Investigation Plan, without a serious deterioration in health, is not considered a serious adverse event. | Serious electrocution  Serious injury of eye from laser |
| Device Deficiency | Inadequacy of an investigational medical device related to its identity, quality, durability, reliability, safety or performance. This may include malfunctions, use error, or inadequacy in the information supplied by the manufacturer. | Device presents misleading information |
| Adverse Device Effect (ADE) | Adverse event related to the use of an investigational medical device.  NOTE 1: This includes any adverse event resulting from insufficiencies or inadequacies in the instructions for use, the deployment, the implantation, the installation, the operation, or any malfunction of the investigational medical device.  NOTE 2: This includes any event that is a result of a use error or intentional abnormal use of the investigational medical device. | As device deficiency  Patient face knocked with device whilst aligning. |
| Serious Adverse Device Effects (SADE) | Adverse device effect that has resulted in any of the consequences characteristic of a serious adverse event. | As SAE.  Device falls onto patient requiring hospitilisation |
| Unanticipated Serious Adverse Device Effect (USADE) | Serious adverse device effect which by its nature, incidence, severity or outcome has not been identified in the current version of the risk analysis report.  NOTE: Anticipated SADE (ASADE): an effect which by its nature, incidence, severity or outcome has been previously identified in the risk analysis report. | Photo induced epileptic seizure. |

The CI will investigate all adverse events and reactions and grade and record them in the patients CRF. Any patient who has an adverse reaction will be referred to either the Accident and Emergency Department or the St. Paul’s Primary Eye Care Department of the RLUH within LUHFT or to their General Practitioner depending on the situation. The monitoring of the reporting of adverse events and reactions will be undertaken by a study steering committee chaired by Consultant Ophthalmologist, Mr [name]

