## Inclusion criteria

Patients, male or female, aged 12 years and above with a diagnosis of either keratoconus or Fuchs endothelial corneal dystrophy (FECD)/ corneal lamellar surgery and subjects with no corneal disease (healthy volunteers).

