## Exclusion criteria

In this study, patients who have poor fixation or have a learning disability will not be excluded as this will be an opportunity to hopefully demonstrate the advantage of our new LiveOCT device. Exclusion criteria: Nystagmus, under 12 years old, inability to provide informed consent,

1. Study procedures

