## Screening and eligibility assessment

Eligible patients and their guardians (if appropriate) attending the corneal clinics, will initially be approached by members of the direct clinical care team and given an A4 advert for our study. If interested, a simple eligibility assessment will be carried out. If eligible, they will be asked if they would be willing to be contacted by a member of the study team to discuss further. If agreeable, they will be given the participant information sheet (PIS) and told they will be contacted subsequently by an investigator.

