**Table 1: Tests undertaken during each of the three visits.**

|  | **Baseline (month 0)** | **Month 3 Visit** | **Month 6 visit** | **Comments** |
| --- | --- | --- | --- | --- |
| **Eye examination (visual acuity and slit lamp bio microscopy)** | V | V | V | Standard Clinical procedure |
| **Endothelial cell counting (ECD)** | V | V | V | Standard Clinical procedure |
| **Tomography** | V | V | V | Standard Clinical procedure |
| **Tomography** | V | V | V | Standard Clinical procedure |
| **Imaging using our new LiveOCT devices, D1** | V | V | V | Extra test |
| **Imaging using our new LiveOCT device, D2** | V | V | V | Extra test |
| * All the procedures except for imaging by using our new OCT device are part of standard care pathway  * For patients with Keratoconus, all the three visits are standard patient care pathway  * For patients with FECD, month 3 visit is an additional visit to the standard care  * For healthy volunteers, all 3 visits will be research activities | | | | |

1. Study treatments

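### The protocol names a light-induced seizure as a possible serious effect of LiveOCT, but its eligibility text as shown does not ask about seizure history

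*Protocol*

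**What the plan says.** In the Protocol's adverse event and safety reporting section, a table defines the regulatory reporting terms. Its introduction says that "the examples that would apply to the LiveOCT study are presented in the table below". An unanticipated serious adverse device effect (USADE) is there defined as one whose nature, incidence, severity or outcome "has not been identified in the current version of the risk analysis report". The LiveOCT example beside that definition is "Photo induced epileptic seizure".

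Entry to the study is governed by three short pieces of text:

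- Inclusion criteria: "Patients, male or female, aged 12 years and above with a diagnosis of either keratoconus or Fuchs endothelial corneal dystrophy" or corneal lamellar surgery, together with healthy volunteers who have no corneal disease.
- Exclusion criteria: "Exclusion criteria: Nystagmus, under 12 years old, inability to provide informed consent". The list then ends in a comma. The same section deliberately keeps in people with poor fixation or a learning disability.
- Screening and eligibility assessment: "If interested, a simple eligibility assessment will be carried out". Its content is not stated.

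Table 1 has a row for "Imaging using our new LiveOCT devices, D1" and another for D2. Both are ticked at all three visits and marked as extra to standard procedure.

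**The concern.** Once a protocol names a serious event for its own device, one expects the entry rules either to ask about the history most plainly linked to that event or to explain why this is unnecessary. Here they do neither. The history in question is known photosensitive epilepsy or a previous seizure set off by light.

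LiveOCT imaging is done for research in every group, so a participant with such a history would be exposed without any clinical need for that test. If a seizure did occur, it would be serious for that person. It would also stop the study, because the protocol halts it on any adverse event. No endpoint, sample size or analysis depends on this point. It concerns only who is imaged.

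**Working it through.** No arithmetic applies, so the texts are set side by side.

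1. **Does the protocol link the event to this device?** Yes, as an example. The table's introduction says its examples are ones that would apply to this study. Most entries are plainly device-specific, such as trapped fingers, irritation of the eye from the laser, or the device falling onto a patient. The seizure entry stands in the same column.

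2. **Does any inclusion condition use seizure history?** No. The conditions are age and corneal status only.

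3. **Does any listed exclusion use it?** No. The three items are nystagmus, age under 12 and inability to consent. None of the three refers to seizures or epilepsy.

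4. **Does screening use it?** Not as stated. The eligibility assessment has no described content beyond being simple.

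5. **Does any other text fill the gap?** Seizure and epilepsy appear nowhere else in the text shown. Medical history is a case report form topic under Data collection tools and source document identification, but no rule there links it to eligibility. The Monitoring section plans a risk assessment before initiation but states no resulting exclusion.

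6. **Test case.** Take a 20-year-old with keratoconus and known photosensitive epilepsy, without nystagmus and able to consent. This person meets the inclusion criteria, meets none of the listed exclusions, and faces no stated screening question that would bring the epilepsy to light. A healthy volunteer with the same history passes in the same way.

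7. **Is the exposure research-only?** For LiveOCT, yes, at every visit and in every group. Other procedures also fall outside usual care for some participants; for example, "For patients with FECD, month 3 visit is an additional visit to the standard care". The seizure example is attached to LiveOCT, however, so those procedures do not add to this point.

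**The case against.** The strongest reply is that too much is being asked of an illustration. The table explains reporting categories and is not a hazard assessment. It also lists electrocution, and the section opens by saying that the team expects no adverse events. On this view the entry shows how a remote event would be classified, and it names an event, not a group of people at risk. This stands as far as it goes. A reader might infer that the protocol acknowledges LiveOCT to be a seizure hazard, and the documents do not support that: they give no wavelength, flicker, brightness or exposure data, and no evidence that the light can provoke a seizure.

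A reader might also infer that calling a pre-named event unanticipated is a mistake. That cannot be shown either. The label depends on the risk analysis report, which is not available. The definition also turns on incidence, severity and outcome as well as nature, so naming an event in advance does not by itself contradict it.

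A third inference to avoid is treating the number of scans or the minutes of session time as a measure of harm. They describe scheduling, and light exposure is not given.

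There are also general safeguards. The direct care team makes the first approach, consent must explain risks, a risk assessment and regulatory clearance come first, and testing stops if a participant is distressed. These are real, but none is a rule that keeps a person with this history from being imaged. The exclusion list may have lost an item after its trailing comma, and the consent pages are not shown. If a seizure exclusion was lost there, restoring it is part of the same fix.

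**Conclusion.** The point holds in a limited form. The protocol gives a light-induced seizure as a LiveOCT example of a serious device effect, and its eligibility text as shown would still admit a person with known photosensitive epilepsy to research-only imaging. The risk cannot be sized from the documents: neither the chance of a seizure nor the number of such people among the 90 planned participants is given.

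The conclusion assumes that the exclusion list is complete as shown and that no seizure question sits in material not shown. On that footing it is a cheap improvement of optional severity, made as a precaution. It is not a finding that participants face a demonstrated danger.

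**What to change.** Three small changes:

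1. In Screening and eligibility assessment, add one question on photosensitive epilepsy or any previous light-induced seizure.
2. In Exclusion criteria, complete the list and add: *known photosensitive epilepsy or a previous light-induced seizure excludes a person from LiveOCT imaging, unless the risk analysis documents that the light stimulus cannot provoke seizures.*
3. In the risk assessment already planned before initiation (Monitoring), check the seizure example against the risk analysis report. If the report already identifies the event, list it as an anticipated serious device effect. If it does not, assess it there.

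The cost is one question, one conditional line and one cross-check within work already planned. The downside is that a few otherwise eligible people would be excluded, which slightly narrows an entry policy meant to be broad. That the number is small is an assumption, since the documents give none. These people would be identified before enrolment, so they can be replaced and the group sizes of 40, 30 and 20 need not change. If the risk analysis clears the light stimulus, the exclusion falls away and nobody is turned away.
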